## 1.2 Rationale

Although various guidelines exist providing evidence-based recommendations on psychosocial care in cancer [Jacobsen 2012], evidence suggests that many patients with cancer who might benefit from these interventions do not receive them [Jacobsen 2015]. This fact formed the basis for an implementation study (HuCare), funded by the Ministry of Health and by the Lombardy Regional Health Trust, conducted in 28 cancer centers nation-wide, completed in 2014. This project evaluated the feasibility of a strategy (the “HuCare Quality Improvement Strategy - HQIS), aimed at integrating into practice 6 psychosocial interventions, recommended by international guidelines. The strategy, based on context analysis and problem solving, includes communication skills training for clinical staff and the support by an external team, to assist staff in identifying obstacles, finding solutions, and strengthening

motivation to carry out recommended changes. HuCare has demonstrated the strategy's feasibility in a real context [Passalacqua 2016], since over 75% of patients had received the psychosocial interventions in 27 of the 28 participating centers.

Building on the findings of HuCare, this randomized trial was therefore designed to

Assess whether the introduction of the HQIS in oncology wards improves the quality of life of cancer patients. This trial is based on the following hypotheses.

- improving communication and relational skills of clinical staff (medical oncologists and nurses) facilitates change of behavior
- providing support for context analysis and for the solution of problems detected at a local level favors implementation of recommended psychosocial interventions
- carrying out such recommendations improves quality of life of cancer patients who initiate active treatment, i.e. who are at high risk of experiencing a decrease in their HRQoL.

The study follows the methodology outlined in the Medical Research Council guidelines on complex interventions [Craig 2008], in the CONSORT Statement and its extensions (Patients Reported Outcomes (PRO) Extension and Extension to Cluster Randomised Trials) [[www.equator-network.org](http://www.equator-network.org)].

## 2. Objectives and ENDPOINTS

### 2.1 Primary objective

The primary objective is to assess the effectiveness of the HQIS vs standard care, in terms of improvement of at least one of the two functional domains of HRQoL, emotional or social, detected at baseline (before treatment initiation) and at clinical follow-up (approximately 3 months after study enrolment).

The primary endpoint will be measured using the EORTC QLQ-C30 questionnaire (see Paragraph 8.1), version 3.0 validated into Italian.

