| OBJECTIVES        | 
Primary objective is to evaluate effectiveness of HQIS vs standard care, in terms of improvement of at least one of two functional domains (emotional or social) of Health-Related Quality of Life (HRQoL), detected at baseline (before treatment initiation) and at clinical follow-up (after about 3 months). Primary endpoint will be measured with the EORTC QLQ-C30 questionnaire, version 3.0 validated into Italian.
 
Secondary objectives are:
 
 
a) To investigate whether the strategy's effect lasts through time (long-term effect), impacts on specific patient categories, modifies global HRQOL or only given domains, reduces mood disorders
 
b) To measure implementation rate in participating centers, in terms of percentage of clinical staff members (medical oncologists and nurses) who complete training, percentage of patients with unmet psychosocial needs and percentage of patients who systematically receive the strategy
 
 |
| STUDY DESIGN      | multicenter, Stepped-Wedge, Cluster Randomized Trial (SWD-CRT), where the strategy is carried out sequentially in three clusters (each comprising 5 centers) and in three equally spaced epochs. Implementation sequence will be randomly determined and by the end of the trial all centers will have implemented the HQIS strategy. The intervention is applied at a cluster level, and assessed at an individual level (on patients).                                                                                                                                                                                                                                                                                                                                                                                                                                                                                                                                                                                        |

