### **8.6 Sample Size**

The number of subjects to be enrolled was defined following the methodology for incomplete, cross-sectional Stepped-wedge cluster randomized trials [Hussey 2007, Hemming 2013, Hemming 2014; Hemming 2016] considering:

- a) 3 clusters, each comprising 5 centers and with equal size for each cluster (capacity of enrolment per week);
- b) an expected mean difference deemed clinically acceptable lying between 3 and 8 points of at least one domain (social or emotional), values indicated in the paper by Cocks et al [Cocks 2011], as minimal clinically relevant differences for the domains of this study;

- c) an ICC (Intra-class correlation coefficient) equal to 0.80, as reported in two papers [Uwer 2011, Lundy 2014 ];
- d) the Wald Test, with time as fixed effect and cluster as the random effect [Hussey 2007]
- e) a power of 80% and two-tail alpha of 5%;
- f) drop-out of 20% at follow-up [Ledderer 2013].

Applying the *steppedwedge* di STATA/MP 11.2 procedure [Hemming 2014] we calculated an overall sample size of 720 patients, which means 60 patients in each cluster for every detection period.

|            | t1  | t2  | t3  | t4  | t5  |
|------------|-----|-----|-----|-----|-----|
| c3= 5 unit | 60  | 60  | 60  |     | 60  |
| c2=5 unit  | 60  | 60  |     | 60  | 60  |
| c1 =5 unit | 60  |     | 60  | 60  | 60  |
|            | 180 | 120 | 120 | 120 | 180 |

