## 8.7 Statistical analysis

Sample descriptive characteristics will be presented as means and standard deviation (SD) when normally distributed, or as medians and interquartile ranges (IQR). Although the majority of responses to individual items/symptom/functional scale of the EORTC QLQ-C30 questionnaire exhibits asymmetric distribution, findings will nevertheless be described with both mean and median values.

The main unit of analysis is the individual. Differences of HRQoL values between the two groups, post-intervention and control, relative to each of the two functional domains (emotional or social) of interest for the primary objective, will be analyzed using a binomial Beta regression model (BB), as suggested by different authors [Khan 2015, Arostegui 2012], due to the asymmetric distribution of values. This model also enables to estimate the strategy's effect in terms of Odds Ratio, the preferred measure by oncologists for its more immediate interpretation and greater usefulness in clinical practice, compared with HRQoL absolute values [Khan 2015]. To carry out the analysis with the BB model, responses will be transformed into a scale (0,1) by using the formula  $Y-a / b-a$ , where a and b are the lowest and highest possible scores, respectively, and Y is the observed response. For instance, a score of 80 will be expressed as  $80-0/(100-0) = 80/100 = 0.8$ .

Since the study is an incomplete, cross-sectional stepped-wedge cluster randomized controlled trial (with an implementation period) the following covariates will be included in the model: the implementation epoch (first, second or third) and time of exposure to the strategy; the cluster the patient belongs to (1, 2 or 3) and intra-cluster correlation [Hemming 2015, Stat Med].

The demographic and clinical variables which influence the outcome with a *p value* < 0.20 in the univariate analysis will be included in the regression model. Data analysis will be conducted using SAS v 8.1 and STATA/SE 11.2

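### Success needs improvement in only one of two separately analysed domains, but the protocol gives one unsplit 5% alpha and no multiplicity rule

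*Protocol*

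**What the plan says.** - **Success rule.** Section 2.1 states the primary objective "in terms of improvement of at least one of the two functional domains of HRQoL, emotional or social". The synopsis repeats it: "improvement of at least one of two functional domains (emotional or social".
- **Analysis.** Section 8.7 compares post-intervention and control values "relative to each of the two functional domains (emotional or social) of interest for the primary objective", with a beta-binomial regression. The two domains are not combined into one test, and the section sets no significance threshold.
- **Error rate.** The only alpha is in the input list of section 8.6: "a power of 80% and two-tail alpha of 5" per cent. In the same list the effect to be detected is "an expected mean difference deemed clinically acceptable lying between 3 and 8 points of at least one domain (social or emotional".
- **Multiplicity.** Nothing in the protocol says how the 5% is shared between the two domains.
- **SAP.** Section 8 announces an SAP, to be defined before database lock. Its listed contents include the statistical methods but do not name multiplicity.
- **Number of domains.** One sentence in section 8.1 speaks of three domains. The objectives, the sample size and the analysis all name two.

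**The concern.** An either/or rule over two separate analyses gives the trial two chances of a positive primary result. If each chance is taken at the full 5%, the primary conclusion carries a larger error than the one alpha in the plan suggests. A positive finding in a single domain would then be open to challenge.

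The success rule and the sample-size alpha are both fixed in the protocol. If the alpha is divided later, the stated power no longer belongs to the test that will be run.

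**Working it through.** **Inputs from the protocol.** Two primary domains with an either/or rule (2.1, 8.7); two-sided alpha 5% and power 80% (8.6); 720 patients (8.6).

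**Assumptions, not in the protocol.** Each domain is tested at two-sided 5%. The two test statistics are bivariate normal with correlation ρ under no effect. No ρ is given, so a range is shown.

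**1. The plan's own figure.** Three clusters, each observed in four epochs, with 60 patients per cell: 3 × 4 × 60 = 720. The count agrees. The power behind it cannot be reproduced, because no standard deviation is given and the effect is a range of 3 to 8 points. The steps below take 80% power at 5% as stated.

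**2. At least one false rejection, either direction.** For independent tests this is 1 − 0.95² = 0.0975. In general it is 1 − P(|Z₁| ≤ 1.960 and |Z₂| ≤ 1.960).

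**3. At least one false claim of improvement.** Each test puts 2.5% in the direction of benefit. For independent tests this is 1 − 0.975² = 0.0494. In general it is 1 − P(Z₁ ≤ 1.960 and Z₂ ≤ 1.960).

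| ρ | Any false rejection | False claim of improvement |
|---|---|---|
| 0 | 9.75% | 4.94% |
| 0.3 | 9.51% | 4.76% |
| 0.5 | 9.07% | 4.54% |
| 0.7 | 8.35% | 4.17% |
| 0.8 | 7.81% | 3.90% |
| 0.9 | 7.04% | 3.52% |
| One test at 5% | 5.00% | 2.50% |

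The first column drops below 8% at a correlation of about 0.76.

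**4. Effect of a split.** At 2.5% two-sided per domain the critical value is 2.241. The chance of any false rejection is then 4.94% at ρ = 0, 4.65% at 0.5 and 4.02% at 0.8, so it stays within 5%.

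**5. Price of the split when only one domain responds.**
- Detectable difference at unchanged size: (2.241 + 0.842)/(1.960 + 0.842) = 1.100, about 10% larger.
- Power at unchanged size and effect: Φ(1.960 + 0.842 − 2.241) = Φ(0.560) = 71.2%, against 80%.
- Size needed to keep 80%: 1.1005² = 1.211, and 720 × 1.211 ≈ 872, or 872/12 ≈ 73 per cell instead of 60.

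If both domains respond, the chance of success in at least one is higher than for one domain alone, so these are the least favourable figures.

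**6. If there were three primary domains.** For independent tests, 1 − 0.95³ = 14.3%. The size of the primary family therefore matters.

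**The case against.** The strongest reply has three parts.

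- **The 5% is a planning input.** It stands in the sample-size list, and section 8.7 sets no threshold for either domain. This is correct. Testing each domain at 5% is inferred, so every inflated figure is conditional on that reading.
- **The SAP may supply the rule.** Section 8 leaves the statistical methods to a document that is not shown, and multiplicity procedures are often placed there. A reader might infer that the trial has no adjustment at all; the protocol alone cannot show that. The reply still does not close the point. If the SAP adds no adjustment, the error is inflated. If it tests at 2.5% per domain, 720 patients sized at 5% no longer give the stated power for an effect in one domain. In either case something in the protocol needs restating.
- **The two-sided figure overstates the risk of a false success.** A reader might infer that the trial's false-positive rate simply is 8-10%. That range needs a correlation no higher than about 0.76, and it counts rejections in the direction of harm, which cannot satisfy a rule based on improvement. Both scales come from the same questionnaire and the same patients, so independence is best treated as an upper bound. For a false claim of improvement the rate stays below 5%, although it is well above the 2.5% that one two-sided 5% test allows.

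**Conclusion.** The point holds in conditional form. Followed as written, an either/or rule on two separately analysed domains, with one unsplit alpha and no multiplicity rule, does not hold the primary conclusion at 5%.

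If each domain is tested at two-sided 5%, the overall two-sided error lies between about 7.0% (correlation 0.9) and 9.75% (independence). The error in the direction of benefit is 1.4 to 2 times the nominal 2.5% (3.52/2.5 = 1.4; 4.94/2.5 = 2.0). These figures rest on the inferred per-domain level, the normal approximation and an assumed correlation. The documents do not support an unconditional rate, nor the statement that the protocol prescribes 5% per domain.

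**What to change.** - **Section 8.7.** State that the emotional and social domains are tested with the Holm procedure (or Hochberg) at an overall two-sided 5%, and report adjusted p-values. A hierarchy or a global test would also control the error; what matters is that one rule is fixed in advance.
- **Section 8.6.** Keep 720 patients and restate the planning figures at 2.5% per domain. For an effect in one domain only, give either the detectable difference (about 10% larger) or the power (about 71% instead of 80%). Add that the loss is smaller if both domains respond.
- **Section 8.1.** Reconcile the mention of three domains with the two named elsewhere, so that the primary family is unambiguous.

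The text cost is a sentence or two in each section. The statistical cost is the loss of power just given. Restoring 80% for a single-domain effect would take about 872 patients, which is hard to fit with enrolment limited to two index weeks per epoch. Accepting and stating the lower power is therefore the more practical course.

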### 2.2 Secondary objectives

a) To investigate whether the strategy has an effect:

- on patient mood
- in the long-term
- on overall HRQoL or on specific domains
- on specific patient types (case-mix)

b) To measure implementation rates, in terms of:

- percentage of clinical staff who complete training (see paragraph 5)
- percentage of eligible patients who systematically receive the strategy

### 3. STUDY DESIGN

This is a multicenter, incomplete stepped-wedge cluster randomized controlled trial (SWD-CRT) (since data are not collected during implementation), where the intervention strategy is sequentially carried out in three groups of centers (clusters with 5 centers each) and in three equally spaced periods of time (every 4 months, from 2nd to 4th epoch). The study also includes an initial epoch during which none of the centers is exposed to the intervention, and a final epoch when all centers will have implemented the strategy [Hemming 2015, BMJ; Hemming 2015, Stat Med]. The implementation epoch for each center is randomly assigned, and by the end of the study, all centers will have received the strategy. The intervention is applied at a cluster level, which constitutes the unit of randomization, and assessed at an individual level, (on the patients of each cluster) with cross-sectional model (for each period, patients are different).

| Centers   |    | Epoch 1 (Months 1-4) | Epoch 2 (Months 5-8) | Epoch 3 (Months 9-12) | Epoch 4 (Months 13-16) | Epoch 5 (Months 17-20) |
|-----------|----|----------------------|----------------------|-----------------------|------------------------|------------------------|
| Cluster 1 | 1  | Control              | HQIS Implementation  | Post-Intervention     | Post-Intervention      | Post-Intervention      |
|           | 2  | Control              | HQIS Implementation  | Post-Intervention     | Post-Intervention      | Post-Intervention      |
|           | 3  | Control              | HQIS Implementation  | Post-Intervention     | Post-Intervention      | Post-Intervention      |
|           | 4  | Control              | HQIS Implementation  | Post-Intervention     | Post-Intervention      | Post-Intervention      |
|           | 5  | Control              | HQIS Implementation  | Post-Intervention     | Post-Intervention      | Post-Intervention      |
| Cluster 2 | 6  | Control              | Control              | HQIS Implementation   | Post-Intervention      | Post-Intervention      |
|           | 7  | Control              | Control              | HQIS Implementation   | Post-Intervention      | Post-Intervention      |
|           | 8  | Control              | Control              | HQIS Implementation   | Post-Intervention      | Post-Intervention      |
|           | 9  | Control              | Control              | HQIS Implementation   | Post-Intervention      | Post-Intervention      |
|           | 10 | Control              | Control              | HQIS Implementation   | Post-Intervention      | Post-Intervention      |
| Cluster 3 | 11 | Control              | Control              | Control               | HQIS Implementation    | Post-Intervention      |
|           | 12 | Control              | Control              | Control               | HQIS Implementation    | Post-Intervention      |
|           | 13 | Control              | Control              | Control               | HQIS Implementation    | Post-Intervention      |
|           | 14 | Control              | Control              | Control               | HQIS Implementation    | Post-Intervention      |
|           | 15 | Control              | Control              | Control               | HQIS Implementation    | Post-Intervention      |

**Figure 1 – Study design: stepped wedge cluster randomized controlled trial**

The cluster randomized design was selected because the intervention is organizational and requires high involvement of all center staff; therefore, randomizing individual oncologists or patients would not be possible, as it would entail a high risk of contamination bias. Furthermore, the stepped-wedge design enables to overcome the logistic difficulty of simultaneously providing the intervention to all centers, and it is ethically acceptable, since it ensures that all patients may receive an intervention considered to be beneficial. Finally, the SWD-CRT offers the opportunity to measure the effect of the intervention in time (secondary objective), which is one of the gaps highlighted in the literature [Ament 2014, Passalacqua 2016].

## 4. STUDY POPULATION

### 4.1 Setting

The project was presented in October 2015 at the national conference of the Italian Association of Medical Oncology (AIOM), during a meeting open to interested members. Study recruitment was performed using the “Facilities Questionnaire”, a brief survey developed for the project to ascertain the presence of essential prerequisites for study conduction (Attachment I), and to ensure representativeness of centers according to size and geographical location. The number of centers to be included has been determined based on feasibility (costs and logistic restrictions) and clusters defined geographically (North, Center-South, Islands).

The Directors of participating wards declared that all staff was informed on the aims and conduction of the project and accepted to take part in the study.

### 4.2 Study patients

Cancer outpatients of any type and stage, who consecutively access the participating centers during an index period and who fulfill the following eligibility criteria:

#### Inclusion criteria

Patients with cancer, of any type and stage, who consecutively access participating centers in an index period and who satisfy the following eligibility criteria:

- Age  $\geq$  18 years
- Diagnosis (histological or cytological) of solid cancer notified to the patient within two months
- Who are about to start a new medical treatment: chemotherapy (both I.v. and oral), molecular target drugs, hormonal therapy, immunotherapy.
- Expected survival  $>$  3 months
- Good comprehension of the Italian language
- Who have read, understood, and signed the informed consent

#### Exclusion criteria

- Previous chemotherapy or other medical cancer treatment
  - Enrolment in the same trial in a previous epoch
  - Simultaneous participation to other trials which entail self-administration of questionnaires/scales measuring anxiety, depression or quality of life (Patients Reported Outcomes, PROs)
    - Hospitalized
    - Treated for psychiatric disorders
    - Affected by mental or psychiatric disorders, due to cancer or coexisting illness, which interfere with awareness or judgement ability
- Inability to complete the questionnaire or to comply with 3-month follow-up

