### c) Implementation of recommendations

Together with training (recommendation 1), 5 more recommendations for the psychosocial care of patients, identified in the HuCare project, will be implemented at each center by trained staff and with the support of the IT.

After the first visit with the oncologist, and before initiation of treatment, all “new” patients will receive the following activities, aimed to satisfy their information needs and to facilitate communication with the oncologist:

- The oncologist encourages the patient to use a question prompt list (recommendation 2), to favor communication. The tool was created in the framework of the HuCare project, by cross-cultural adaptation [Caminiti 2010] (Attachment III). The oncologist also introduces to each patient his or her specialist nurse (recommendation 3), who will accompany the patient through his/her care.
- The specialist nurse provides the patient with the two self-administered questionnaires, HADS and NEQ, validated into Italian (see paragraph 8), to detect psychological distress (recommendation 4) and social needs (recommendation 5). For patients with distress and/or social needs, necessary counselling and/or services (psychologist, psychiatrist, social worker, etc.) are activated, according to a written procedure defined at each center before the implementation phase begins. The specialist nurse also offers the patient a meeting at the Point of Information and Support (PIS), a space reserved for patients, equipped with internet access and information material. The PIS should be adjacent to the oncology offices, in a location ensuring privacy (recommendation 6).

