### **7.1 Eligibility assessment**

After the first consultation with the oncologist and before initiation of the first cycle of therapy, outpatients consecutively accessing the center will be screened by the oncologist over a period of two index weeks, indicated by the statistician. To this end, the oncologist checks the presence of all inclusion criteria and absence of all exclusion criteria, introduces the study to eligible patients, provides the information sheet and collects the informed consent to participation before initiation of the first cycle of therapy.

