### **11.1 Informed consent**

This study does not imply any type of experimental pharmacological treatment, or changes to diagnostic –therapeutic practice. Since the HQIS is implemented at each center regardless of patient informed consent signature, eligible patients will be asked to consent to the handling of their personal data. The informed consent form will be dated and signed by the patient and by the physician, authorized in accordance with regulations of the center's local EC. Information sheet and consent form for data handling will be used also for the feasibility study.

The informed consent form prepared by the coordinating center may be modified following specific requests of the local ECs. A copy of the signed informed consent shall be given to the patient and the original version retained by the center's investigator as part of the study documentation. It is the investigator's responsibility to obtain written informed consent to the use of health information. If a patient chooses not to continue with the study, it is the investigator's responsibility to ensure that no more health data of this person are collected. All gathered data will be used in the final analysis.

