### Criteri di esclusione

|                                                                                                                                                                                        | Si [1]                | No [2]                |
|----------------------------------------------------------------------------------------------------------------------------------------------------------------------------------------|-----------------------|-----------------------|
| 1. Pregressa chemioterapia o altro trattamento medico per tumore                                                                                                                       |  |  |
| 2. Arruolato nel medesimo trial in un periodo precedente                                                                                                                               |  |  |
| 3. Partecipazione in atto ad altri trial che prevedono la misura di PRO                                                                                                                |  |  |
| 4. In trattamento da uno psicologo o psichiatra o con antidepressivi                                                                                                                   |  |  |
| 5. Ricoverato in degenza ordinaria                                                                                                                                                     |  |  |
| 6. Presenza di condizioni patologiche mentali o psichiatriche, dovute al tumore o a patologie concomitanti, che interferiscono con lo stato di coscienza o con la capacità di giudizio |  |  |
| 7. Impossibilità a completare il questionario o a garantire il follow-up a tre mesi                                                                                                    |  |  |

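### The psychiatric-treatment exclusion is undated and worded two ways, so care triggered by HQIS can exclude some distressed patients in post-intervention epochs whose control-epoch counterparts would more often be enrolled

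*Protocol*

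**What the plan says.** **The exclusion.** The list in protocol section 4.2 has "Treated for psychiatric disorders". Item 4 of the exclusion list on the data collection form (Attachment IV) and the general practitioner letter (Attachment VI) have instead "In trattamento da uno psicologo o psichiatra o con antidepressivi", that is, under a psychologist or psychiatrist, or on antidepressants. None of the three says when the treatment must have begun.

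**What HQIS does.** Under section 5 c), the patient activities take place "After the first visit with the oncologist, and before initiation of treatment". They include distress and needs screening with HADS and NEQ, after which: "For patients with distress and/or social needs, necessary counselling and/or services (psychologist, psychiatrist, social worker, etc.) are activated". They do not depend on trial participation; section 11.1 says "Since the HQIS is implemented at each center regardless of patient informed consent signature".

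**When eligibility is checked.** Section 7.1: "After the first consultation with the oncologist and before initiation of the first cycle of therapy, outpatients consecutively accessing the center will be screened", over two index weeks, which section 8.4 says are randomly selected.

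**Order for an enrolled patient.** Section 7.2 places the baseline record and questionnaires ahead of the patient-directed recommendations.

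**The concern.** An eligibility criterion should mean the same thing in every epoch. Here one of the services that HQIS activates is also, at least on the form's wording, a reason for exclusion, and both operate between the first oncology visit and the first cycle. Where HQIS reaches a patient before the eligibility check does, the strategy influences who can enter the trial.

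The patients affected would be distressed ones, who are likely to score low on emotional function. That is one of the two primary domains, and HQIS is aimed at these patients. Section 6 also plans subgroups by baseline anxiety and depression, which would be thinned in one condition only. Patients screened out never enter the analysed population of section 8.8, so no missing-data analysis can recover them.

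**Working it through.** No figure in the protocol depends on this point, so there is nothing to reproduce. The check is of the sequence of events, followed by an illustration of size.

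**1. Sequence**

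| Patient | Control epoch | Post-intervention epoch |
|---|---|---|
| First visit inside the index weeks | Eligibility, consent, baseline | Eligibility, consent, baseline, then HQIS activities (7.1, 7.2). A later referral does not remove the patient |
| First visit before the index weeks, first cycle not yet given, attends during them | No HQIS referral; enrolled unless usual care has already led to treatment | HQIS screening and referral may already have happened (5 c, 11.1); if in care, the undated exclusion can apply |

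Only the second row differs between conditions. Section 7.1 does not require the first consultation to fall inside the index weeks, and section 4.2 allows a diagnosis notified up to two months earlier. Attachment I asks centres to confirm a psychologist on at least two days a week, so care could start before the first cycle.

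**2. Size**

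Suppose a share r of otherwise eligible post-intervention patients is excluded, and their mean score lies D points below the mean m of the rest.

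- Mean with them: (1 − r)m + r(m − D) = m − rD
- Mean without them: m
- Shift: r × D

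The share r is itself a product: (first seen before the index weeks) × (distressed) × (already in care at screening). The protocol gives none of these, nor D. All are assumptions.

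| r | D = 20 | D = 30 |
|---|---|---|
| 0.3 × 0.4 × 0.2 = 0.024 | 0.48 | 0.72 |
| 0.05 | 1.0 | 1.5 |
| 0.10 | 2.0 | 3.0 |
| 0.15, e.g. 0.5 × 0.4 × 0.75 | 3.0 | 4.5 |

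A second parameterisation uses p = share distressed, D = their deficit against non-distressed patients, and f = share of distressed patients excluded only post-intervention:

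shift = D × [p − p(1 − f)/(1 − pf)]

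For p = 0.3, D = 25, f = 0.25: 25 × [0.3 − 0.225/0.925] = 1.42 points. Over p = 0.2 to 0.4 and D = 15 to 25:

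| f | Shift (points) |
|---|---|
| 0 (the 7.2 order holds for everyone) | 0 |
| 0.10 | 0.2–0.6 |
| 0.25 | 0.6–1.7 |
| 0.50 | 1.3–3.8 |

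The yardstick is the 3 to 8 point difference in section 8.6.

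**3. Can the model remove it?**

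A shift present in every post-intervention cell and absent from every control cell has the same pattern as the treatment indicator. In a linear model with period and cluster terms it passes unchanged into the effect estimate. In the planned beta-binomial model it would move the odds ratio in the same direction.

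**4. Direction**

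For 3-month levels, removing low scorers raises the post-intervention mean and favours HQIS. For change from baseline, it removes patients with the most room to improve and may work against HQIS.

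**The case against.** The strongest objection is section 7.2. Eligibility and consent come before baseline, and baseline before the HQIS activities, so a patient handled as written is checked before HQIS can refer them and the shift is zero. This stands for patients met during the index weeks. A reader might infer that the design as a whole screens distressed patients out of the post-intervention epochs; the documents do not support that.

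For patients seen earlier, it can be argued that section 7.2, applied strictly, bars everyone whom HQIS has already reached, distressed or not, so that the loss is not selective. That is a fair reading. But section 7.2 orders procedures and is not an eligibility criterion. The only rule in section 4.2 that bears on such a patient is the undated exclusion, applied by an oncologist who is not blinded (8.5). Nor does the protocol say that earlier-seen control patients are to be left out as well.

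Other points that stand:

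- Section 4.2 alone covers psychiatric treatment; seeing a psychologist for distress need not count. That route rests on the form and the letter. These also differ from the body on age and time since diagnosis, so they may be out of date.
- Usual care may refer too. Attachment I asks about psychologist availability and about existing routine screening of psychological needs. The control patient is therefore more often enrolled, not always.
- Dating the criterion alone would admit patients whose baseline follows HQIS exposure, against section 7.2. The remedy needs a sequencing rule as well.

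**Conclusion.** The point holds as a limited risk of differential selection. It is confined to patients first seen before the index weeks and not yet treated, and is clearer on the form's wording than on that of section 4.2. Its size is unknown. With r between 2.4% and 10% and D between 20 and 30, it is about 0.5 to 3 points, so from small to the lower end of the target difference. The larger values in the tables require half of all distressed patients to be excluded, or 15% of all otherwise eligible patients, and nothing in the protocol points to that.

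A reader might also infer a bias in favour of HQIS throughout. The protocol supports that direction only for 3-month levels. Section 2.1 frames the objective as improvement assessed at baseline and follow-up, and for change scores the direction is uncertain.

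It is worth correcting because the safeguard costs almost nothing, whereas selection at entry cannot be undone in the analysis.

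**What to change.** 1. Reconcile the exclusion in section 4.2 with item 4 of the form and with the general practitioner letter, so that one wording applies.
2. State in section 4.2 and on the form that the criterion refers to treatment already in place at the first oncology visit, in all epochs. Care activated by HQIS is then not a reason for exclusion.
3. State in section 7.1 that eligibility and baseline are completed before any HQIS screening or referral, and apply the same first-visit rule in control and post-intervention epochs. This keeps step 2 consistent with section 7.2.
4. Record the start date of any such care, and report exclusions by reason and epoch so that any imbalance can be seen.

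The cost is a clause in each place, one date field, and possibly a few patients first seen before the index weeks who are not enrolled; the protocol does not give their number. The planned total of 720 does not change.
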